## Abstract

**Introduction:**

Currently, the majority of women worldwide with threatened preterm birth are treated with tocolytics. Although tocolytics can effectively delay birth for 48 hours, no tocolytic drug has convincingly been shown to improve neonatal outcomes and effects on long-term child development are unknown. The aim of this follow-up study of a placebo controlled randomised trial is to investigate the long-term effects of atosiban administration in case of threatened preterm birth on child’s neurodevelopment and behaviour development, overall health and mortality.

**Methods and analysis:**

This protocol concerns a follow-up study of the multicentre randomised double-blind placebo controlled APOSTEL 8 trial (NL61439.018.17, EudraCT-number 2017-001007-72). In this trial, women with threatened preterm birth (between 30 and 34 weeks of gestation) defined as uterine contractions with (1) a cervical length of <15 mm or (2) a cervical length of 15–30 mm and a positive fibronectin test or (3) in centres where cervical length measurement is not part of the local protocol: a positive fibronectin test or Actim-Partus test or (4) ruptured membranes, are randomised to atosiban or placebo for 48 hours. The primary outcome is a composite of perinatal mortality and severe neonatal morbidity. Children born to mothers who participated in the APOSTEL 8 study (n=760) will be eligible for follow-up at 4 years of corrected age and assessed using four parent-reported questionnaires. Primary outcomes are neurodevelopment and behaviour problems. Secondary outcomes are on child growth and general health. All outcomes will be compared between the atosiban and placebo group with OR and corresponding 95% CI. Analyses will be performed using the intention-to-treat approach.

**Ethics and dissemination:**

The Medical Research Ethics Committee from Amsterdam UMC confirmed that de Medical Research Involving Human Subjects Act (Dutch WMO-law) did not apply to our study (W21_386 # 21.431). Results will be published in a peer-reviewed journal and shared with stakeholders and participants. This protocol is published before analysis of the results.

STRENGTHS AND LIMITATIONS OF THIS STUDYThis study will be a long-term follow-up study of the multicentre randomised double-blind placebo controlled APOSTEL 8 trial.This study will evaluate the effect of atosiban versus placebo in threatened preterm birth between 30 and 34 weeks of gestation on long-term child outcomes at 4 years of age concerning overall health, neurodevelopment and behaviour.For this follow-up study, three validated questionnaires will be used to evaluate child outcomes, including the Ages and Stages Questionnaire-3, Strengths and Difficulties Questionnaire and Vineland screener in combination with a questionnaire on overall health.Although less accurate than face-to-face evaluation, these parental questionnaires are useful as screening tools to detect child development and behaviour problems.

## Background

 In 2018, the WHO reported that preterm birth is the leading cause of death worldwide for children under the age of 5 years.^1^ Although various pharmacological agents and therapeutic interventions have been developed to reduce occurrence of preterm birth, preterm birth rates remain high.^2 3^ Apart from mortality, preterm birth can lead to both severe short-term and long-term neonatal morbidity, including neurodevelopmental disorders, respiratory problems and impaired ophthalmological functions.^4^,^7^

In case of threatened preterm birth, administration of tocolytics drugs is widely spread and has been part of standard care in many countries for decades. Treatment with tocolysis can delay imminent preterm birth to allow a complete course of antenatal corticosteroid administration hereby promoting fetal lung maturation and facilitating transfer to a hospital with neonatal intensive care unit (NICU) facilities.^8^,^10^ Various tocolytic drugs have shown to be effective in delaying delivery, including atosiban, however, no tocolytic drug has proven to be effective in reducing neonatal morbidity and mortality compared with a placebo.^11 12^ Therefore, the current use of tocolytic drugs in case of threatened preterm birth is insufficiently supported by available evidence. For this reason, our research group started the double-blinded randomised controlled Assessment of Perinatal Outcome after Specific Tocolysis in Early Labour (APOSTEL) 8 trial in 2017. This trial evaluates the effectiveness of atosiban versus placebo administered for 48 hours in women with a diagnosis of threatened preterm birth between 30 and 34 weeks of gestation on neonatal morbidity and perinatal mortality.^13^

Besides the effects on the immediate neonatal period before hospital discharge, it is essential to extend our scope on long-term child’s health and developmental outcomes since pregnancy interventions can have unexpected harmful long-term effects.^14^,^18^ However, thus far only a few randomised trials concerning tocolytic drug administration during pregnancy have performed long-term follow-up on child development. Our research group conducted the APOSTEL II trial, comparing nifedipine maintenance therapy to placebo in case of threatened preterm birth between 26 and 32 weeks of gestation.^19^ At 2 years of age, we found a higher rate of fine motor problems in the nifedipine group (n=78) (22.2% vs 7.6%), but lower rate of poor problem-solving (21.2% vs 29.1%) compared with the placebo group (n=66).^20^ We concluded that there was insufficient evidence to support use of nifedipine for maintenance tocolysis. Second, the APOSTEL III trial compared tocolysis with nifedipine versus atosiban in threatened preterm birth between 25 and 34 weeks of gestation.^21^ Follow-up at 2.5–5.5 years showed composite abnormal development in 30% of children in the nifedipine group (n=115) and 38% in the atosiban group (n=110).^22^ Neither nifedipine nor atosiban was considered as preferred treatment in women with threatened preterm birth on both short-term and long-term outcome. A recent population-based cohort study including 600 children reported no difference in neurodevelopmental outcomes at 5.5 years among children with and without antenatal exposure to tocolysis by atosiban or nifedipine. However, follow-up outcomes were retrospectively obtained and the population solely concerned pregnancies complicated by preterm prelabor rupture of membranes between 24 and 32 weeks gestation.^23^

In conclusion, long-term effects of tocolytic drug administration during pregnancy on child outcomes are still largely unknown. We will, therefore, perform a follow-up study of the randomised placebo-controlled APOSTEL 8 trial. This follow-up study aims to determine the long-term effects of atosiban versus placebo in threatened preterm birth on neurodevelopment, behaviour problems and general health of children around 4 years of corrected age. The APOSTEL 8 follow-up will help to identify potential beneficial or harmful effects of atosiban administration during pregnancy and will contribute to further improving threatened preterm birth healthcare.

## Methods and analysis

### Study setting

This study will be a follow-up study of the APOSTEL 8 study, an international, multicentre, randomised, double-blinded, placebo-controlled trial performed across 30 hospitals situated in the Netherlands, UK and Ireland (NL61439.018.17, EudraCT-number 2017-001007-72). The APOSTEL 8 trial includes women with threatened preterm birth between 30 and 34 weeks of gestation. Threatened preterm birth is defined as uterine contractions with (1) a cervical length <15 mm; (2) a cervical length of 15–30 mm with a positive fetal fibronectin test; or (3) a positive fibronectin test or insulin-like growth factor binding protein-1 (Actim-Partus test) in centres where cervical length measurement is not part of local protocol or (4) ruptured membranes. Eligible women are randomised to atosiban or placebo (0.9% saline) for 48 hours. The primary outcome is a composite of adverse perinatal outcomes including perinatal mortality and six severe perinatal morbidities: bronchopulmonary, periventricular leukomalacia >grade 1, intraventricular haemorrhage >grade 2, necrotising enterocolitis ≥stage 2, retinopathy of prematurity >grade 2 or needing laser therapy, andculture-proven sepsis. Secondary outcomes include various infant and maternal outcomes which can be found in the published protocol. The APOSTEL 8 started in 2017 and complete recruitment in 2023. Long-term follow-up of the APOSTEL 8 study was announced in the original trial protocol.^13^ This long-term follow-up study is directed at the children born to mothers who participated in the APOSTEL 8 trial, therefore, either exposed to atosiban or placebo during pregnancy. We will use four parent-reported questionnaires to assess neurodevelopment, behaviour problems and general health. Data collected in the original trial will be linked to the data obtained in this follow-up study. The study protocol has been developed according to the Standard Protocol Items: Recommendations for Interventional Trials criteria.

### Participants/eligibility criteria

Children of both singleton and multiple pregnancies, born to mothers who participated in the APOSTEL 8 trial, will be eligible for inclusion. Assessment will be performed when children are around 4 years of corrected age (ideally between 3 years and 9 months (3;9) to 4 years and 3 months (4;3) years of corrected age). Participants who did not give consent to be approached for follow-up research in the original APOSTEL 8 trial, will not be approached in this follow-up study. Also, participants included in the UK or Ireland will not be eligible for inclusion.

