#### (Neuro)development

The third version of the Ages and Stages Questionnaire (ASQ-3) will be used to assess neurodevelopment. The ASQ-3 is a screening tool to monitor child development by measuring five domains: communication, gross and fine motor skills, problem-solving skills and personal-social skills and can be used till 6 years of age. The ASQ-3 is the most commonly used parent-reported screening tool on development worldwide and is validated in a Dutch reference population.^24^

Interpretation: scores of ≥1 SD below the mean of the ASQ normative data in two or more domains or ≥2 SD below the normative mean in at least one domain will be considered abnormal. A score of ≥1 and <2 SD below mean in one domain will be considered as mildly abnormal.

The Vineland screener is a tool developed in the Netherlands to assess adaptive functioning in children up to 6 years of age. Adaptive functions refers to how well a person copes with common demands in life. The tool consists of 72 questions concerning everyday behaviour and covers four domains: communication, social, motor and daily living skills. The total adaptive functioning score is the sum of these four domains.^25 26^

Interpretation: A score between the 11th and 25th percentile of the population is considered mildly abnormal (77–84 for children of 3–4 years of age and 100–107 for children 4–5 years of age). A score ≤10th percentile of the population is considered as abnormal (≤76 for children of 3–4 years of age, ≤99 for children of 4–5 years of age).

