#### Interpretation

Growth: we will present height as a continuous and dichotomous outcome (normal/abnormal score). An abnormal score is defined as 1.6 SDS above or below target height range based on parental height Dutch reference values.^33^ We will calculate the body mass index (BMI) and will report BMI as a continuous outcome and as a proportion of children who are underweight, overweight or obese based on Dutch reference data.^34 35^Health-related problems: we will report on medical conditions, hospital admissions, medication (used) and history of surgery.

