#### Statistical analysis

Differences in baseline characteristics of APOSTEL 8 follow-up participants will be compared between atosiban and placebo group using unpaired t-test, Mann-Whitney U test, χ^2^ test or Fisher’s exact test when appropriate. A two‐sided p<0.05 will be considered statistically significant. To detect potential attrition bias, baseline characteristics of follow-up participants will be compared with those lost to follow-up.

For the main outcomes, neurodevelopment and behaviour, we will report mean scores with SD and dichotomous outcomes (abnormal/mildly abnormal) of the domains and total score of the ASQ-3, Vineland screener and SDQ. For general health-related outcomes, we will report on the outcomes as previously described. For the outcome mortality, the denominator needs to be changed into all children born to participants of the original APOSTEL 8 trial.

For the main analysis, all outcomes will be analysed using generalised linear mixed effects model to enable accounting for the dependence of multiple pregnancies. For continuous outcomes, this will provide mean difference with 95% CI and for dichotomous outcomes OR with 95% CI. All analyses will be performed according to the intention-to-treat principle and complete case analysis using SPSS or R (latest version).

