#### Additional sensitivity analyses

In accordance with the APOSTEL 8 trial, the following subgroup analyses are planned:

Singleton and multiple pregnancy separately.Cervical length <15 mm vs cervical length 15–30 mm and a positive fibronectin test (or no

cervical length measurement and a positive fibronectin test or Partus test).

Ruptured vs intact membranes at entry.Previous preterm birth.Excluding children that exceed the optimal window of 3;9 years–4;3 years of corrected age. In sensitivity analyses, we will use imputation techniques to impute missing outcome data for children lost to follow-up. Multiple imputation techniques will only be applied when it can be assumed that data are missing at random and the follow rate is >70%. the follow-up rate is lower than 70, a best-case and worst-case scenario analyses will be performed.Composite outcome of deceased children or survived children with abnormal cognitive and/or behaviour development. Combining mortality data with survival of children with a severe developmental disability will help in providing the full scope of relevant outcomes from the start of randomisation until up to 4 years of age. The denominator in this analyses will be all children born in the APOSTEL 8 trial, instead of the number of children included in follow-up. However, this outcome has some challenges due to the high probability of loss to follow-up (as is the case in many obstetrical follow-up studies after several years), and therefore, the inevitable need to deal with missing data. This will be done by either applying multiple imputation techniques or, in case of a high loss to follow-up, a worst-case and best-case scenario analyses.

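### Continuous outcomes are compared with no stated allowance for age at completion, although the age window is only a target and the Vineland total rises steeply with age

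*Protocol article*

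**What the plan says.** Under Participants/eligibility criteria, the protocol article places the assessment around 4 years of corrected age, "ideally between 3 years and 9 months (3;9) to 4 years and 3 months (4;3) years of corrected age". It sets no minimum or maximum. Under Additional sensitivity analyses, one listed item is "Excluding children that exceed the optimal window of 3;9 years–4;3 years of corrected age", so the main analysis keeps these children.

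Table 1 (Outcomes) lists the ASQ-3, Vineland, SDQ, height and BMI as a mean with SD, followed by dichotomised categories. Its footnote on age and gender applies to cut-offs. Statistical analysis describes a generalised linear mixed model whose stated purpose is to handle the dependence in multiple pregnancies, and adds: "For continuous outcomes, this will provide mean difference with 95% CI". No age term is named.

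The (Neuro)development section gives the Vineland cut-offs by year band. Abnormal is "≤76 for children of 3–4 years of age, ≤99 for children of 4–5 years of age", and mildly abnormal is "77–84 for children of 3–4 years of age and 100–107 for children 4–5 years of age". The same section says the screener is meant to "assess adaptive functioning in children up to 6 years of age". No number is printed for a child aged 5 or over.

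**The concern.** The plan deals with age where it dichotomises and says nothing about age where it compares means. If a score grows with age and children complete the questionnaires at different ages, part of the spread in that score is simply age. That widens the confidence interval for the mean difference. The sample cannot be enlarged to compensate: Sample size fixes the maximum at the children of the parent trial and expects about 400, or 200 per group. If completion age also differed systematically by arm, the difference would appear as a developmental or growth effect.

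A smaller gap is that Vineland feeds the composite, yet its numeric cut-offs stop at age 5 while the age window has no upper end.

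**Working it through.** **The plan's own power figure.** Sample size states 80% power with 200 per group for a 12-point difference (two-sided pooled Z-test, alpha 0.05), without a base rate. Taking 30% against 18% as an assumption gives 80.5%. This figure concerns the composite, which rests on age-specific cut-offs, so the age question leaves it unchanged.

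**Inputs from (Neuro)development.** Vineland 10th percentile: 76 (3–4 years) and 99 (4–5 years). Upper end of the mildly abnormal range, the 25th percentile: 84 and 107.

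**Assumptions.** Normal scores, a linear age trend, completion ages uniform over the stated range, clustering ignored.

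1. SD = (84 − 76) / (1.2816 − 0.6745) = 8 / 0.6071 = 13.2. The 4–5 year band gives the same (107 − 99 = 8).
2. Age slope = 99 − 76 = 107 − 84 = 23 points per year, and 23 / 13.2 is about 1.7 SD per year.
3. A uniform age range of s years adds an SD of 23 × s / √12. Total SD = √(13.18² + added SD²). Effective n per arm = 200 / variance ratio.
4. Power uses an illustrative true difference of 0.28 SD (0.28 × 13.18 = 3.69 points), which 200 per arm detects with 80% power once age is removed: power = Φ(3.69 / (total SD × √(2/200)) − 1.96).

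| Completion ages | Added SD | Total SD | Variance ratio | Effective n per arm | Power |
|---|---|---|---|---|---|
| Age removed | 0 | 13.2 | 1.00 | 200 | 80% |
| 3;9–4;3 | 3.3 | 13.6 | 1.06 | 188 | 77.5% |
| 3;6–4;6 | 6.6 | 14.8 | 1.25 | 160 | 71% |
| 3;0–5;0 | 13.3 | 18.7 | 2.02 | 99 | 51% |

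**Sensitivity to the SD.** The 13.2 comes from year-wide bands and may already contain a year of age spread (6.64 points). Removing it gives √(13.18² − 6.64²) = 11.4, and the three increases become roughly 8%, 34% and 136%. The table is therefore not an exaggeration on this count.

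**The other outcomes.** Behaviour problems gives SDQ cut-offs of 16 and 17 for abnormal below and above age 4, a shift of 1 point. By the same method the SD is 3 / (1.2816 − 0.8416) = 6.8, so the slope is about 1 / 6.8 = 0.15 SD per year, roughly a twelfth of the Vineland slope. The document gives no figures from which a slope for ASQ-3, height or BMI can be derived.

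**Chance imbalance in completion age.** The SE of the arm difference in mean age is (12 × s / √12) × √(2/200) months: 0.17 for s = 0.5, 0.35 for s = 1 and 0.69 for s = 2. A one-month difference would shift the Vineland contrast by 23 / 12 = 1.9 points (0.15 SD). It lies 5.8, 2.9 and 1.4 SEs out respectively, so chance will not produce it in the target window.

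**The case against.** The strongest reply is that the primary outcome is hardly touched. The composite is built from dichotomies with age- and gender-specific cut-offs, and the power calculation rests on it. A reader might infer that the primary analysis mixes ages. It does not; the point is confined to the continuous comparisons. This part of the reply stands.

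Second, the article does not say the means are unadjusted. It names no covariate for age, and covariate lists are often left to an analysis plan. Height may be meant as an SDS, since the article uses SDS when defining abnormal height. That is fair, and the point is limited accordingly. Still, the article specifies how age enters the cut-offs and describes the model for the means without it, so a sentence is needed somewhere.

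Third, a reader might infer that a child over 5 cannot be classified on Vineland. The documents do not support that. Abnormal is defined generally as at or below the 10th percentile of the population by age and gender, and the tool serves children up to 6 years. Only the printed number is missing. Nor does the article say that any child will be assessed after the fifth birthday, although Background reports an earlier follow-up by the same group at 2.5–5.5 years.

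Fourth, bias is not the natural reading. Blinding is retained, contact is made in the same way in both arms, and timing is by corrected age. Chance imbalance is already covered by the confidence interval. A response-related difference by arm cannot be excluded with about 50% follow-up, but nothing in the article points to one.

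Finally, the planned analysis restricted to 3;9–4;3 brings the loss down to about 6%. It does so by discarding children, whereas adjustment keeps them.

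**Conclusion.** The point holds as one of avoidable lost precision in the continuous comparisons, chiefly the Vineland total. The size depends on the actual spread of completion ages, which the article does not give: about 6% extra variance if all children fall evenly in the target window, 25% over one year, and about 100% over ages 3 to 5. These figures rest on normal scores and a linear trend of 23 points per year. They should not be carried over to the SDQ, where the implied age effect is small, or to ASQ-3, height and BMI, where none can be computed from the document. The primary composite and its sample size are unaffected. The missing Vineland number from age 5 is a gap in wording and does not leave the outcome undefined.

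**What to change.** In Statistical analysis, state that the models for continuous Vineland, ASQ-3 and SDQ scores include exact corrected age at completion and sex as covariates, or that age-standardised scores are analysed. State that height and BMI are analysed as age- and sex-standardised SDS.

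In (Neuro)development, state which Vineland norm applies from age 5. This is preferable to excluding children of 5 and over from the composite, which would discard outcome data in a study that already expects to lose half its sample.

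The cost is wording and slightly more analysis work. One caveat is that completion age is measured after randomisation. Tabulating it by arm would show whether adjustment raises any question of interpretation; with blinding and timing by corrected age, none is expected.

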### Study design

The APOSTEL 8 follow-up study will be performed within the Dutch consortium for Healthcare Evaluation and Research in Obstetrics and Gynaecology (NVOG Consortium; https://zorgevaluatienederland.nl/NVOG). Good clinical practice trained researchers from the Amsterdam University Medical Center will cross-check medical records and Dutch Personal Record database of both mother and child(ren) for the possible occurrence of death. Thereafter, information letters and informed consent forms of this follow-up study will be sent by email to the APOSTEL 8 participants. Contact details of the research team are shared in the information letter to facilitate the opportunity to ask potential questions or discuss concerns. If the email address is unknown, participants will be contacted by phone and informed consent forms will be sent by mail. After giving informed consent, participants are redirected to the online questionnaire via a web link. Participants can withdraw participation at any time.

